# mHealth intervention (mTB-Tobacco) for smoking cessation in people with drug-sensitive pulmonary tuberculosis in Bangladesh and Pakistan: protocol for an adaptive design, cluster randomised controlled trial (Quit4TB)

**DOI:** 10.1136/bmjopen-2024-089007

**Published:** 2025-02-25

**Keywords:** Digital Technology, Tuberculosis, Tobacco Use, Smoking Reduction, Behaviour

## Abstract

**Introduction:**

People with tuberculosis (TB) who continue to smoke are more likely to have poor health outcomes than those who quit. Established smoking cessation approaches such as mHealth may help patients with TB quit smoking. This paper summarises the methodology proposed to assess the effectiveness and cost-effectiveness of mTB-Tobacco (an mHealth intervention) in helping patients with TB stop smoking and have improved health outcomes.

**Methods and analysis:**

A two-arm, parallel, open-label, multicentre, cluster randomised, two-stage adaptive design trial is proposed to first evaluate the superiority of mTB-Tobacco, compared with usual care and then the non-inferiority of mTB-tobacco compared with face-to-face behaviour support. Study settings include TB treatment centres in Bangladesh and Pakistan. The study population includes adult patients, newly diagnosed (within 4 weeks) with pulmonary TB disease, daily smokers, willing to quit and have access to mobile phones. The primary outcome includes biochemically verified continuous smoking abstinence assessed at 6 months per Russell Standard. A generalised linear mixed-effects model will be used to assess the impact of mTB-Tobacco intervention on continuous outcomes, incorporating fixed effects for the intervention, random effects for clusters and relevant covariates. Cost-effectiveness analysis will be done to estimate the cost per quitter and cost per quality-adjusted life year gained, calculate the incremental cost-effectiveness ratios to establish the value for money for mTB-Tobacco.

**Ethics and dissemination:**

This trial will be conducted in compliance with International Council on Harmonisation - Good Clinical Practice guidelines and the Declaration of Helsinki. The study has been approved by the ethics committees of the University of Edinburgh Medical School Research Ethics Committee (EMREC) of UK, the Bangladesh Medical Research Council (BMRC) and the National Bioethics Committee (PMRC) of Pakistan. The results of this trial will be disseminated in peer-reviewed journals and presented in academic conferences.

**Trial registration number:**

ISRCTN86971818 (https://doi.org/10.1186/ISRCTN86971818); pre-enrolment, submission date: 29 August 2023; registration date: 11 September 2023.

STRENGTHS AND LIMITATIONS OF THIS STUDYThis is the first trial evaluating effectiveness and cost-effectiveness of mHealth-based mTB-Tobacco intervention to help patients with tuberculosis (TB) quit smoking.The superiority phase of the trial will allow us to establish the effectiveness of mTB-Tobacco intervention compared with usual care.The non-inferiority phase of the trial will allow us to establish that the mTB-Tobacco intervention is atleast as effective as behaviour support therapy.The self-report of primary outcome of abstinence at 6 months will be biochemically verified by performing carbon monoxide (CO) breath tests using CO monitors.Limitations of the mTB-Tobacco intervention include its lack of interactivity, as the SMS messages sent to patients with TB are unidirectional. Additionally, patient’s ability to read and understand the SMS messages may also pose a limitation.

## Introduction

 Tuberculosis (TB) is an infectious disease with high morbidity, mortality and economic burden. Despite being preventable and curable, TB remains the world’s second leading cause of death from a single infectious agent in 2022 the first being coronavirus disease (COVID-19). The Global Tuberculosis Report 2023 states that in 2022, there were 7.5 million reports of newly diagnosed TB, which is the highest in history, perhaps due to diagnosis and treatment delays faced during the COVID-19 pandemic, and 1.3 million deaths.^1 2^ The majority of the TB burden remains concentrated in low and middle-income countries (LMIC), including Pakistan and Bangladesh. A downward trend in TB burden has been noticed in all WHO regions, but the decline is not sufficient to end the global TB epidemic within the timelines set to achieve Sustainable Development Goals (SDGs).^3^

Among five major attributable risk factors including malnutrition, HIV infection, smoking, alcohol use and diabetes, 0.7 million new TB cases are attributable to tobacco smoking alone, especially in males because in most LMICs, males have much higher smoking prevalence than females.^4^ A meta-analysis conducted in 2022 to assess the effect of smoking on TB treatment outcome concluded that smoking increases the chances of poor treatment outcome by 51% (OR=1.51, 95% CI 1.30 to 1.75, I² 75.1%), where the effect was even higher for LMIC (OR=1.74; 95% CI 1.31 to 2.30).^5^ Another meta-analysis concluded that smokers had greater odds of unfavourable outcomes (pooled OR=1.23, 95% CI 1.14 to 1.33), delayed sputum conversion (pooled OR=1.55, 95% CI 1.04 to 2.07) and loss to follow-up (pooled OR=1.35, 95% CI 1.21 to 1.50).^6^

In terms of tobacco use, 1.3 billion people globally use tobacco in one or more forms, and 80% of them live in LMIC, while the prevalence of tobacco smoking is 19.3% worldwide, which is an established attributable factor for TB.^7^ A dual burden of TB and tobacco use in these countries makes it imperative to devise strategies that address both of these conditions. Literature shows that there are significant benefits of quitting smoking on TB treatment outcomes. Those who quit smoking may have better TB cure rates (91% vs 80%, p<0.001), lower TB relapse rates (6% vs 14%, p<0.001) and higher sputum smear conversion at 2 months (91% vs 87%, p=0.036), than as compared with those who continue to not quit smoking, respectively.^8^ This makes smoking cessation in patients with TB a public health priority. There is a need for evidence-based smoking cessation approaches^9^ and increasing policy support to help patients with TB quit smoking.^10^

Smoking prevalence in patients with TB is higher than the general population,^11^ but the vast majority of patients with TB are neither routinely asked about their smoking status nor advised to quit.^12^ There are well-established pharmacological and non-pharmacological interventions developed and tested for effectiveness to help patients with TB quit smoking. Previous randomised controlled trials (RCT) in Bangladesh and Pakistan have shown that face-to-face behavioural interventions are effective for smoking cessation, reporting quit rates as high as 41% at 6 months.^13^ Despite recognising the benefit of quitting and ownership of the problem by policymakers, the integration of smoking cessation in routine TB care remains challenging because of health system-related barriers including insufficient human resources, cost, reach and sustainability,^14^ thus no TB high-burden countries have so far integrated face-to-face smoking cessation within TB services.

Recognising the challenges of integrating and scaling up face-to-face interventions, the WHO developed an mHealth smoking cessation package (mTB-Tobacco) that can be delivered as SMS messages via mobile phones to patients with TB.^15^ It is anticipated that delivering the mHealth package will cost less than resource-intensive face-to-face behavioural interventions, but it is unknown if this package is as effective and therefore more cost-effective than face-to-face behavioural intervention. Hence, there is a need to first establish the effectiveness of mHealth intervention in terms of helping patients with TB to quit smoking. The Quit4TB trial is designed to assess the effectiveness and cost-effectiveness of mTB-Tobacco in achieving continuous abstinence for at least 6 months and improving health outcomes in people with TB who smoke daily.

## Methods and analysis

### Trial design

The Quit4TB trial is a two-stage adaptive design, multicentre, cluster RCT (cRCT) consisting of four phases as shown in figure 1.

Phase 1 involves consultations with a patients and public involvement (PPI) group about the study processes. PPI members will review and provide feedback on the SMS text messages translated into local languages as well as the participant information sheet and consent forms. For this, a PPI group of eight members will be formed including patients with TB (n=3), their family members (n=3), health care professional (n=1) and public representative (n=1), who will be voluntarily recruited from the TB site. Translated study materials will be discussed with them individually or as a group. Debriefing will be done after PPI engagement, and necessary adjustments will be made based on the feedback.

**Figure 1 F1:**
[figure not shown]
Study design and phases of the Quit4TB trial. PPI, patients and public involvement; TB, tuberculosis.

Phase 2 consists of a pilot study, which aims to assess the feasibility of the mTB-Tobacco intervention and other trial processes. The mTB-Tobacco web-based intervention will be pilot tested with a total of 16 participants, 8 each from Bangladesh and Pakistan, that is, 4 in the intervention and 4 in the control arm, in each of Bangladesh and Pakistan. The pilot data will be evaluated using two sets of data, users’ self-reported experiences and their real-time engagement with the programme. Users’ experiences will be collected at a 9-week follow-up through face-to-face interactions. Key questions will focus on users’ experience of taking part in the mTB-Tobacco programme; the clarity, quantity, timing and frequency of messages; what was good about the programme and what was not; completion or non-completion of the programme; and any effect on their attitudes or target behaviour(s). Users’ real-time engagement will be evaluated using computer records from the programme used for launching mTB-Tobacco. The pilot study will be embedded in the next phase of the study, by continuing the pilot study participant’s follow-up up to 6 months, and will be treated with the same processes and governance as the main trial participant data.

Phase 3 will be the superiority trial, which will last for 12 months (6 months recruitments and 6 months follow-ups), to assess effectiveness and cost-effectiveness of mTB-Tobacco (intervention A) compared with usual care (control).

Phase 4 will be the non-inferiority trial that will be conducted if in phase 3 the mTB-Tobacco intervention turns out to be effective in helping patients with TB quit smoking as compared with control. Phase 4 will then last for another 12 months (6 months recruitment and 6 months follow-ups) to compare mTB-Tobacco (intervention A) with the face-to-face behavioural support (intervention B) to assess if it’s as effective as the face-to-face behavioural support intervention to help patients with TB quit smoking. All new patients with TB will be enrolled in phase 4, none of whom will be previously enrolled in phase 3 of the trial.

The trial flow chart is given in figure 2, followed by a written explanation of various aspects of the trial.

**Figure 2 F2:**
[figure not shown]
Quit4TB trial flow chart. CO, carbon monoxide; CRF, case report form; FU, follow-up; MUAC, mid-upper arm circumference; TB, tuberculosis.

### Study settings

This trial will be conducted in Bangladesh (Dhaka division) and Pakistan (Punjab province) simultaneously. A prespecified number of clusters (TB centres) will be selected from each country to recruit study participants.

#### Eligibility criteria for inclusion of clusters

All TB centres with a minimum turnover of 50 new patients with TB per month will be eligible for selection, to make sure that adequate participant enrolment targets are achieved. The included sites must be functioning and designated TB diagnostic centres approved by the National/Provincial TB Control Programme (NTP). These may include primary, secondary or tertiary care health centres (HCs), generally known as the district or tehsil headquarter hospitals in Pakistan. In Bangladesh, health facilities will be the directly observed therapy (DOT) corners at upazila (subdistrict) health complex and urban DOT corners. In addition, the facility must be able to nominate a site focal person (an NTP personnel, for example, the district TB coordinator or the responsible TB clinician at the site) who assumes responsibility for the proper conduct of the trial at their site; the health facility should have an adequate number of qualified staff and adequate facilities for the foreseen duration of the trial to conduct the trial properly and safely, and the HC should be willing to join the trial and provide required administrative support. Facilities not meeting the inclusion criteria will not be eligible for the trial.

#### Study participants

Patients with TB presenting at selected TB centres (clusters) will be screened for inclusion in the trial as per the following eligibility criteria.

#### Eligibility criteria for inclusion of participants

Participants aged 15 years or older, diagnosed with drug-sensitive pulmonary TB (smear positive or negative) in the last 4 weeks, currently smoking tobacco daily or have only stopped or reduced smoking (less than daily) since diagnosed with TB, willing to quit tobacco use, have access to personal mobile phone and willing and able to provide written informed consent (online supplemental file 1) will be included in the study. A smoker in this trial will be defined as ‘a TB patient who smokes cigarette, and/or biddi, and/or water pipe sessions daily, which means at least 25 days in last month; this does not include heated tobacco products for example, e-cigarettes’. A smoker, as per the mentioned definition, also using smokeless tobacco will be eligible to participate in the trial. Informed consent will be taken from adult participants (18 years and above), while assent along with parent/guardian’s consent will be taken for adolescent participants (15–17 years of age). Exclusion criteria include patients anticipated to have adverse effects either due to the study treatment or research burden. These will include those who are/have less than 15 years of age, retreatment TB, multidrug-resistant TB, miliary or extrapulmonary TB, currently using any pharmacotherapy for tobacco dependence and unwilling or unable to provide written informed consent.

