### Randomisation

Since the interventions will be delivered at the group level, this trial is designed as a cluster cRCT where TB centres will be randomly allocated to the different trial arms. The TB centres (clusters) would be randomised in a 2:2:1 ratio to mTB-Tobacco (intervention A), face-to-face (intervention B), or standard care (Control). An independent statistician, blinded to clusters, will identify and use computer-generated random number lists to generate the allocation sequence. The allocation will be based on using minimisation to ensure balance across the groups on the average number of patients with TB seen per month and geographical locations (Bangladesh and Pakistan).

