### Blinding

In this study, we used a blinding methodology to guarantee that specific key individuals remained uninformed about the allocation of treatments. The allocation sequence will be determined by an independent statistician, who has no knowledge of the participating facilities. Nevertheless, as the SMS receipt is a noticeable component, participants will be able to determine whether they are receiving the SMS or not. Therefore, it is not possible to achieve total blindness at the participant level in this circumstance. In addition, the principal investigator (PI) and the research teams are aware of the specific cluster assigned to each treatment group. However, steps will be taken to potentially prevent the data analyst from knowing the treatment assignments in order to reduce bias during the analysis of the data. Thus, the blinding in this trial will occur during randomising the clusters to intervention or control by an independent statistician and also at the level of data analyst while analysing the data.

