### Study assessments

All study participants will have assessments on day 0, week 9 and month 6 time points corresponding with routine TB clinic visits. All the trial activities will be performed by field RAs (one RA per site) who will be hired and trained to take patient consent, collect baseline data, follow-up data and perform study assessments. The trial assessment schedule, given as table 2, outlines the visit dates necessary for data collection, but the patient may be seen more frequently for routine clinical care as needed. During the treatment period, if study participants are unable to attend on the day, every effort would be made to complete the visit within 2 days of the scheduled date. If a scheduled visit is missed without notice, then the RA should endeavour to contact the patient by phone or by home visit.

**Table 2 T2:** Participant enrolment and follow-up assessment schedule for Quit4TB trial

Assessment	Screening	Day 0 baseline	Week 9	Month 6
Assessment of eligibility criteria	⌧			
Written informed consent	⌧			
Face-to-face/phone-based interaction			⌧	
Self-reported tobacco use/abstinence status		⌧	⌧	⌧
CO measurement				⌧
Sociodemographic information		⌧		
Tobacco use and quit history		⌧		
Nicotine dependency		⌧	⌧	⌧
Economic outcomes		⌧		⌧
Process outcomes (fidelity)			⌧	⌧
Medication (TB) compliance			⌧	⌧
Adverse events review			⌧	⌧
TB outcomes				⌧

CO, carbon monoxide; TB, tuberculosis.

During the follow-up phase, scheduled assessments will be carried out no more than 5 days before the scheduled visit. Scheduled visits will be rescheduled to allow for public holidays or other unavoidable circumstances that affect the scheduled visit date, but the rescheduled visit should be no more than 5 days from the originally scheduled visit date. Participants will also be given a card with the contact details for the trial RA and the clinical TB care team at their site. If a patient is more than 5 days late for a scheduled study visit, an additional visit will be performed as soon as possible, including the appropriate assessments that were specified in the trial schedule for the visit that was missed.

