#### Inferential statistics

A mixed-effects model will be used to assess the impact of mTB-Tobacco on continuous outcomes, incorporating fixed effects for the intervention, random effects for clusters and relevant covariates. Logistic regression within the mixed-effects framework will be used to analyse categorical outcomes, accounting for cluster-level variability and intervention effects for the analysis of data in this cRCT. At the end of phase 3 superiority trial, an interim analysis will be done by an independent statistician to assess the effectiveness of the mTB-Tobacco intervention. The result will decide whether the trial needs to proceed to phase 4 non-inferiority trial or be terminated early. In this study, the missing data patterns will first be examined to determine whether the missingness adheres to patterns of complete randomness, randomness or non-randomness. Multiple imputation, a robust technique that generates multiple data sets with imputed values for missing observations, will be used to address the missing data. As a sensitivity analysis technique, missing data imputation will be used to evaluate the robustness of our findings.^20^ The estimates of the intervention effect will next be compared between analyses carried out with complete case analysis and analyses using imputed data sets. This will improve the validity of the study’s conclusions by enabling an assessment of the effect of missing data on the estimation of intervention effects in this cRCT. Open-source R Project software and JASP Team (2024; V.0.19.3) computer software will be employed as our primary tools for data analysis.

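### Patients appear to be recruited after centre allocation by an assistant who knows the arm, so willingness to quit and smoking status at entry can differ between arms, chiefly in phase 3

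*Protocol article*

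**What the plan says.** The protocol article spreads the relevant statements over several sections.

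- **Randomisation:** "TB centres will be randomly allocated to the different trial arms", in a 2:2:1 ratio (mTB-Tobacco, face-to-face support, control), with minimisation on monthly patient volume and country.
- **Study participants:** "Patients with TB presenting at selected TB centres (clusters) will be screened for inclusion in the trial".
- **Study assessments:** "All the trial activities will be performed by field RAs (one RA per site) who will be hired and trained to take patient consent", and to collect baseline and follow-up data.
- **Blinding:** "the principal investigator (PI) and the research teams are aware of the specific cluster assigned to each treatment group". Blinding is claimed only for the statistician who randomises and for the data analyst.
- **Eligibility criteria for inclusion of participants:** a patient must be willing to quit. The rule takes in daily smokers and also people who have given up or cut down since their TB diagnosis, which may be up to four weeks old. The same section states "Exclusion criteria include patients anticipated to have adverse effects either due to the study treatment or research burden" and then lists what this covers: age under 15, certain forms of TB, current cessation drugs and lack of consent.
- **Trial data management:** screening forms are programmed, and the information sheet and consent form are given once eligibility is settled.

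**The concern.** Randomising centres balances, in expectation, what the centres bring to the trial. It does not balance patients who are chosen later by someone who knows the arm. Willingness to quit is elicited by an assistant who is about to offer active support in one phase 3 arm and only a leaflet in the other. The entry rule also puts together people who have already stopped and people who still smoke daily, and the first group plausibly has the better chance of meeting the month-6 abstinence definition. If the proportions of the two groups differ between arms, the primary outcome moves without any effect of the intervention.

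The phase 3 result is at stake, and it also decides whether phase 4 takes place.

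**Working it through.** **1. Is recruitment after allocation, and by someone who knows the arm?** No sentence gives the sequence, so both points are inferred. Centres are allocated as units, and patients enter as they present. For the later phase the Trial design section says "All new patients with TB will be enrolled in phase 4", with none carried over from phase 3. The article describes no listing of eligible patients before allocation. The single site assistant does all trial activities, which includes screening and consent, and belongs to the research team that knows the arm. No blinded recruiter is described.

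**2. Do the existing safeguards reach the problem?**
- Minimisation covers centre volume and country, not patient characteristics.
- Carbon monoxide verification checks the outcome, not who was enrolled.
- A random centre effect absorbs variation between centres, not a systematic shift between arms.
- A blinded analyst receives the patients already selected.
- Programmed forms standardise what is recorded, but do not make the answers independent of the arm.

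**3. The plan's own phase 3 figures, for scale.** Inputs (Sample size section): 18% against 8%, two arms at 2:1, 90% power, 5% significance, 20% attrition, intracluster correlation 0.02, 27 centres.
- The two-proportion formula with continuity correction gives 195 + 390 = 585.
- 585 × 1.2 = 702, against 704 stated.
- Design effect: 1 + (26 − 1) × 0.02 = 1.50, as stated.
- 704 × 1.50 = 1056, close to the stated 27 × 40 = 1080.

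The planned effect is 18 − 8 = 10 points. The point made here does not depend on the sample size.

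**4. Illustration of a shift in mix.** Let s be the share already stopped at day 0, a their six-month abstinence and b that of the others. An arm's abstinence with no treatment effect is b + s(a − b), so a difference d in s between arms produces a difference d(a − b). The documents give neither a nor b. Assumed: b = 5%, a = 20% or 30%.
- a = 20%: 0.10 × (20 − 5) = 1.5 points, or 15% of the planned effect.
- a = 30%: 0.10 × (30 − 5) = 2.5 points, or 25% of the planned effect.

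Setting the control rate to 8% gives s = 3/15 = 20% or s = 3/25 = 12%. A 10-point excess then means 30% against 20%, or 22% against 12%.

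**5. What shifts of that order do to the phase 3 test.** Take 1080 recruits at 2:1 with 20% lost, so 288 control and 576 intervention patients analysed. The design effect is 1 + 31 × 0.02 = 1.62 (32 analysed per centre) or 1 + 39 × 0.02 = 1.78 (40 recruited per centre). Effective sizes are 178 and 356, or 162 and 324. With no true effect and 8% in control, a normal approximation for two proportions gives these two-sided rejection rates:

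| Spurious shift favouring mTB-Tobacco | Rejection rate |
|---|---|
| 0 points | 5% |
| 1 point | about 6% |
| 2 points | 10–11% |
| 3 points | 17–18% |

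The shifts of 1.5 and 2.5 points fall between these rows. A shift in the other direction would hide a true effect instead.

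**The case against.** The strongest reply is that this is the general hazard of an open-label cluster trial, and that much of what might be built on it has no support. Several parts of that reply stand.

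- A reader might infer from "Exclusion criteria include patients anticipated to have adverse effects either due to the study treatment or research burden" that the assistant may exclude patients according to the arm's treatment. The text does not support that. The list that follows at once is mostly objective, no item names an arm's treatment, and no section gives the assistant power to add exclusions. The opening verb leaves the list formally open, but that is a matter of wording.
- A reader might also infer that the bias could use up much of the 8-point non-inferiority margin. Phase 4 compares two active-support arms, so the contrast between active support and a leaflet is absent. The articles' text offers no mechanism for a difference in willingness between those arms. A calibration to the 8% usual-care rate also does not carry over to a phase with an assumed comparator rate of 18%.
- The size is not known. The rates in the illustration are assumptions, and nothing shows how far the willingness rule would move the already-stopped share.
- Eligibility is settled on a programmed form before the information sheet is given, so part of the protective ordering exists. The assistant still knows the arm at that moment.
- The article condenses a fuller protocol, and question scripts and covariate lists may stand there or in the analysis plan. Their absence is therefore not the complaint. The Inferential statistics section speaks of "incorporating fixed effects for the intervention, random effects for clusters and relevant covariates" in its sentence on continuous outcomes, and its sentence on categorical outcomes names no covariates; neither conflicts with the adjustment proposed.

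The reply does not answer the combination that the article itself fixes: recruiters aware of the arm, an elicited entry criterion, and a population that mixes people who have stopped with people who smoke daily.

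**Conclusion.** The concern holds in limited form. The article's statements, read together, imply recruitment after allocation by staff who know the arm, under an entry rule that lets the baseline mix on a plausibly prognostic factor differ between arms. This matters chiefly for phase 3. The documents show that such a difference can arise, not that it will or which arm it would favour. Under the assumed rates, each 10-point difference in the already-stopped share is worth 1.5 to 2.5 points of abstinence, or 15% to 25% of the planned effect. That is too little to account for a 10-point result alone, but enough to raise the false-positive rate noticeably. The conclusion rests on two inferences (the order of events and the assistant's knowledge of the arm) and on the assumption that having already stopped predicts abstinence at month 6.

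**What to change.** 1. **For recruitment still to come:** screen consecutive registered patients. Record smoking status and willingness to quit with one identical question in all arms. Lock the REDCap screening form before any arm-specific information is given. This builds on the form that the Trial data management section already describes.
2. **For the primary analysis:** include day-0 smoking status (already stopped or reduced, against daily) as a fixed covariate in the mixed-effects logistic model, and settle this before phase 3 data are analysed by arm. Table 2 already schedules self-reported tobacco use at day 0. This step can also serve phase 3, where recruitment began in February 2024 and was expected to take six months, so a change to entry procedures may come too late there.

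The cost is a little more screening-log work, one standard question, a form lock and one model term; a protocol amendment would go to the ethics committees. The gain is partial. The assistant still knows the arm, and adjustment handles only the recorded factor, not unrecorded differences in motivation.
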